### 2.12 Statistical analysis

The normality of continuous variables will be assessed via the Shapiro-Wilk test. Normally distributed data will be presented as mean (standard deviation), whereas non-normally distributed data will be presented as median (interquartile range). For normally distributed continuous variables, independent t-tests or repeated measures ANOVA will be utilized for analysis. For non-normally distributed variables, the Mann-Whitney U test or generalized estimating equations (GEE) will be employed. Categorical data will be expressed as numbers (percentages) and analyzed via the chi-square test or Fisher’s exact test, depending on the expected frequencies. The primary outcome, the WOMAC-pain score at 3 months postoperatively, will be analyzed via a linear regression model, adjusting for baseline variables including HADS scores, PCS scores, baseline WOMAC-pain scores, sex, age, and BMI. Additionally, interactions between the treatment group and baseline scores of HADS, PCS, and WOMAC-pain will also be examined. Covariates with *p*-values <0.10 will be retained in the final model. Secondary outcomes will undergo multiple testing corrections via the Benjamini–Hochberg method, with the false discovery rate (FDR) significance level set at q < 0.05. Odds ratios (OR) and 95% confidence intervals (CI) will be reported where applicable. To ensure the robustness of our primary findings, we will conduct a sensitivity analysis using the bootstrap method. The bootstrap analysis will involve 1,000 resamples to estimate the regression coefficients and their 95% confidence intervals (CIs). This analysis will provide additional validation for the stability of the initial regression results. All results will be analyzed using a modified intention-to-treat approach, including all patients who undergo randomization and for whom relevant data are available. Statistical analyses will be conducted via SPSS software (version 25.0; IBM SPSS). A two-sided *p*-value <0.05 will be considered statistically significant unless specified otherwise for false discovery rate (FDR) corrections. Missing data will not be imputed, and no interim analyses are planned.

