### 2.5 Secondary outcomes

Secondary outcomes will include WOMAC stiffness, function, and total scales; Leeds Assessment of Neuropathic Symptoms and Signs (LANSS) Pain Scale; 36-Item Short Form Health Survey (SF-36); postoperative pain scores; Visual Analog Scale (VAS) sleep scores; postoperative sufentanil consumption; need for rescue analgesia; length of Post-Anesthesia Care Unit (PACU) stay; length of hospital stay; and 90-day mortality.

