### 2.8 Study interventions

In this study, patients will apply an LP5 or placebo patch for 12 h daily on the day before surgery and on postoperative days 1, 2, and 3. The preoperative patch will cover the anticipated incision site, while the postoperative patches will be applied 1.5 cm from either side of the incision. The placebo group will apply a placebo patch, identical in appearance and packaging to the actual medication patch. The lidocaine patches and placebo patches used in this study will be manufactured by Beijing Tide Pharmaceutical Co., Ltd. To maintain blinding, both patients and researchers will remain unaware of group assignments. The patches will be applied by medical professionals who are not involved in patient recruitment or data collection. Randomization will be performed before the study begins by an independent researcher using a computer-generated table of random numbers. Group assignments will be sealed in opaque envelopes to maintain blinding of the investigators, patients, and data analysts, and these envelopes will only be opened after the study is completed. The schedule of patient enrolment, study interventions, and outcome assessments will follow the SPIRIT statement (Table 1). All surgeries will be performed by experienced surgeons who have conducted at least 300 knee arthroplasty procedures prior to the study.

**TABLE 1 T1:** Schedule of patient enrolment, study interventions and outcome assessment.

Time point	Study period								
	Enrolment	Allocation	Post-allocation					Close-out	Follow-up
	Pre-op visit	Pre-op 1 day	Intraoperatively	PACU	24 h post-op	48 h post-op	72 h post-op	Discharged	3 months
Patient enrolment									
Eligibility criteria	×								
Written informed consent	×								
Demographic data	×								
Baseline characteristics	×								
HADS	×								
PCS	×								
Randomization/allocation		×							
Study interventions									
5% Lidocaine Patch		×			×	×	×		
Placebo Patch		×			×	×	×		
Outcome assessment									
WOMAC-Pain Scale	×								×
WOMAC-Stiffness Scale	×								×
WOMAC-Function Scale	×								×
WOMAC-Total Scale	×								×
LANSS									×
SF-36									×
Post-op pain scores					×	×	×		
VAS Sleep score					×	×	×		
Post-op sufentanil use							×		
Need for rescue analgesia							×		
Length of PACU stay				×					
Length of hospital stay								×	
90-day mortality									×
Adverse Events									
Hypotension			×	×	×	×	×		
Hypertension			×	×	×	×	×		
Bradycardia			×	×	×	×	×		
Tachycardia			×	×	×	×	×		

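### Three secondary WOMAC scales are measured before surgery, but the plan names no analysis that adjusts for those values and lets a normality test choose the method

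*Protocol article*

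**What the plan says.** Section 2.5 of the protocol article lists the outcomes at issue: "Secondary outcomes will include WOMAC stiffness, function, and total scales; Leeds Assessment of Neuropathic Symptoms and Signs (LANSS) Pain Scale", among others. Table 1 (in section 2.8) marks "WOMAC-Stiffness Scale", "WOMAC-Function Scale" and the WOMAC total at the pre-op visit and again at 3 months. Each therefore has one baseline value and one post-randomization value. Post-operative pain and VAS sleep scores are marked at 24, 48 and 72 h, with no baseline.

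Section 2.12 gives a specific model to one outcome, the 3-month WOMAC pain score, which "will be analyzed via a linear regression model, adjusting for baseline variables including HADS scores, PCS scores, baseline WOMAC-pain scores, sex, age, and BMI".

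The other continuous outcomes come under a general rule. It starts with "The normality of continuous variables will be assessed via the Shapiro-Wilk test". The two branches are "For normally distributed continuous variables, independent t-tests or repeated measures ANOVA will be utilized for analysis" and "For non-normally distributed variables, the Mann-Whitney U test or generalized estimating equations (GEE) will be employed". The only provision specific to secondary outcomes is "Secondary outcomes will undergo multiple testing corrections via the Benjamini–Hochberg method", at q < 0.05. The section also rules out imputation.

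**The concern.** There are three linked problems.

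- **Baseline values without a planned use.** The pre-operative stiffness, function and total scores will be collected. The same paragraph uses the baseline value for the sister pain scale, but no adjusted analysis is named for these three. Adjustment would give a more precise treatment estimate from data already scheduled.
- **A data-driven effect measure.** A significance test on the trial's own data decides between a comparison of means and a comparison of ranks. The quantity reported for each scale is unknown until the data are seen, and the three scales could be reported on different effect scales within one Benjamini-Hochberg family. The rule also tests the variable itself, whereas the normality assumption of a linear model concerns the residuals.
- **A wrong division for repeated scores.** Repeated measures ANOVA and GEE are both methods for correlated measurements, and normality does not separate them. Standard repeated measures ANOVA also drops any patient with a missing time point, which matters when nothing is imputed.

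At stake are the precision and prespecification of secondary results. The validity of the trial and the primary analysis are not in question here.

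**Working it through.** **The plan's own figure.** Section 2.11 states 57 evaluable patients per group for 0.5 SD, two-sided α = 0.05 and 80% power. A two-sample t-test calculation for 0.5 SD gives 64 per group (63 by the normal approximation). The stated 57 is reproduced with 9/17 = 0.529 SD, the upper end of the quoted 8–9 units over an SD of 17. That is a separate matter. I use 57 per group and 0.5 SD only as a convenient setting, because the protocol states no target effect or power for stiffness, function or total.

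**Inputs.** n = 57 per group; difference 0.5 SD; two-sided α = 0.05 for a single test (section 2.11). The correlation r between the pre-operative and 3-month scores is not given, so I assume a range. Equal SDs at both times are also assumed.

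**Variance of the treatment contrast, relative to an unadjusted 3-month comparison**

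- Unadjusted 3-month comparison: 1
- Change score (the group-by-time test of a two-time repeated measures ANOVA): 2(1 − r)
- ANCOVA on the baseline value: 1 − r²

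Change score minus ANCOVA is 2(1 − r) − (1 − r²) = (1 − r)², which is never negative. Unadjusted minus ANCOVA is r², which is also never negative. So ANCOVA is at least as precise as either alternative at every r.

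**Power.** The standardized effect is 0.5 divided by the square root of the relative variance, entered in a two-sample t-test with 57 per group.

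| r (assumed) | Unadjusted | Change score | ANCOVA |
|---|---|---|---|
| 0.2 | 75% | 55% | 77% |
| 0.3 | 75% | 61% | 79% |
| 0.5 | 75% | 75% | 86% |
| 0.7 | 75% | 93% | 96% |

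Example at r = 0.5: relative variance 1 − 0.25 = 0.75; effect 0.5/√0.75 = 0.577; power 86%. The normal approximation gives values up to about one percentage point higher. For r = 0.2 to 0.5, ANCOVA reduces the variance by 4% to 25%. That is worth 1/0.96 = 1.04 to 1/0.75 = 1.33 times the patients in an unadjusted comparison.

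**Repeated scores at 24, 48 and 72 h.** Suppose 5% of scores are missing at each time; the document gives no rate. If the same patients miss all three, repeated measures ANOVA loses 5% of patients. If missingness is independent across times, it loses 1 − 0.95³ = 14.3%. A mixed model keeps every patient with at least one score.

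**The case against.** A reader might infer that the plan prescribes unadjusted 3-month tests for the three scales and so throws the baseline away. Section 2.12 does not say this. It offers four methods and assigns none of them to a named secondary outcome. Repeated measures ANOVA or GEE could take the pre-operative score as one of two time levels. This objection stands. It does not remove the problem, because the usual group-by-time test is then a change-score test, which is less precise than ANCOVA at every r below 1 and less precise than ignoring the baseline when r is below 0.5.

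A second objection is that section 2.10 refers to a predefined statistical plan, where the model for each secondary outcome would normally be set. That is a fair answer to a complaint about missing detail. But the protocol does not leave the method open: it fixes the Shapiro-Wilk gate and the normal/non-normal split. A later plan must either inherit them or depart from the published text.

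Third, nothing here is invalid. Randomization protects an unadjusted comparison, and its error rate already allows for chance baseline imbalance. The gate is stated in advance and the statisticians are blinded, so it cannot easily be steered toward one arm. Both points stand and limit the weight of this point.

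Fourth, the sizes rest on assumptions. At r = 0.2 the gain is only about two percentage points, and the 14% loss is the independent-missingness case. This stands too.

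**Conclusion.** The point holds in a limited form. The protocol names a baseline-adjusted analysis for WOMAC pain alone. Stiffness, function and total, although measured before surgery, are left to a rule that either does not use that value or uses it no more efficiently than ANCOVA would, and that makes the effect measure depend on the data.

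The size cannot be fixed from the document. With r assumed between 0.2 and 0.5, equal SDs, 57 per arm and a 0.5 SD effect, unadjusted power of about 75% becomes about 77% to 86%. This is not a shortfall against a stated aim, since no power is claimed for these scales, and it is per test, before Benjamini-Hochberg correction. The loss of patients under repeated measures ANOVA is about 5% to 14% if 5% of scores are missing at each time.

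The finding concerns the precision and clarity of secondary outcomes. The change should be made because it costs almost nothing. LANSS and SF-36 are outside the baseline point, because Table 1 schedules them only at 3 months.

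**What to change.** Replace the general rule in section 2.12, for these outcomes, with the following:

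- **WOMAC stiffness, function and total.** For each scale, fit a linear model for the 3-month score on treatment, that scale's own baseline value and centre (the stratification factor in section 2.7). Report the adjusted mean difference with a robust or bootstrap 95% confidence interval, whatever the Shapiro-Wilk result. This is not the primary model, which lists other covariates and does not list centre, so it needs to be written out.
- **Pain and sleep scores at 24, 48 and 72 h.** For each outcome, use one linear mixed model with all available time points, in place of the choice between repeated measures ANOVA and GEE by normality. This needs no imputation and keeps partly observed patients, under the usual missing-at-random assumption.
- **Shapiro-Wilk.** Keep it, if wanted, for choosing descriptive summaries, and not for choosing the test.

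The cost is wording in the protocol or analysis plan, to be settled before unblinding. The baseline scores are already scheduled, and a bootstrap is already planned for the primary outcome. No new data or patients are needed.

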Given the high incidence and refractory nature of CPSP following knee arthroplasty (Beswick et al., 2012), this study aims to test the hypothesis that LP5 can prevent CPSP in patients undergoing knee arthroplasty. This rigorously designed study will evaluate the potential efficacy of lidocaine patches in managing postoperative pain, with a particular focus on their ability to prevent the transition from acute to chronic pain. Through this randomized controlled trial (RCT), we aim not only to provide critical data on the clinical application of lidocaine patches but also to offer new insights for improving future pain management strategies.

This study has several limitations. First, the choice of a 1.5 cm patch distance was based on safety considerations from previous studies and preliminary experiments. Although this distance is considered the safest for orthopedic surgeries, it may not be the optimal distance for analgesic efficacy. Nevertheless, safety is paramount in all clinical treatments. Second, the follow-up period of 3 months may not be sufficient to fully assess the long-term impact of CPSP. We plan to establish a specialized patient cohort for long-term follow-up and further research in this patient population. Additionally, the exclusion of certain patient groups, such as those with long-term opioid use and a history of alcoholism, may limit the generalizability and external validity of the findings. Including these patients in future research is important to provide a more comprehensive understanding of postoperative chronic pain, though their inclusion might introduce significant bias regarding CPSP outcomes.

The primary aim of this randomized controlled trial is to evaluate the effectiveness of the LP5 in preventing CPSP following knee arthroplasty. LP5 will be applied during the early perioperative period, including the day before surgery and postoperative days 1–3. The findings are expected to demonstrate that the use of LP5 may effectively prevent CPSP, reduce acute postoperative pain, and decrease opioid consumption. Additionally, LP5 may facilitate faster postoperative recovery, improving overall patient rehabilitation and quality of life. This study is expected to provide valuable insights for future multimodal analgesia strategies, optimizing postoperative pain management and improving patient outcomes.

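### If repeated-measures ANOVA is used without imputation for the 24/48/72 h pain or sleep scores, a patient missing one reading loses all three; one mixed model on all readings avoids this

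*Protocol article*

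**What the plan says.** Section 2.12 chooses methods for continuous variables by a test on the trial data: "The normality of continuous variables will be assessed via the Shapiro-Wilk test". For variables that pass, "For normally distributed continuous variables, independent t-tests or repeated measures ANOVA will be utilized for analysis". For those that fail, "For non-normally distributed variables, the Mann-Whitney U test or generalized estimating equations (GEE) will be employed". No method is assigned to a named secondary outcome.

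The same section defines a modified intention-to-treat set, "including all patients who undergo randomization and for whom relevant data are available", and states "Missing data will not be imputed, and no interim analyses are planned". The software is SPSS version 25.0.

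Table 1 in section 2.8 marks two continuous outcomes at several times after randomisation: the row "Post-op pain scores" and the VAS sleep row, each at 24, 48 and 72 h. The WOMAC scales are also measured twice, but one of the two occasions is the preoperative baseline. The primary outcome, WOMAC pain at 3 months, has its own linear regression.

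**The concern.** Classical repeated-measures ANOVA needs a full set of readings from each patient. With three scheduled readings and no imputation, a patient seen at 24 and 48 h but not at 72 h contributes nothing. Three consequences follow.

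- **Recorded data are discarded.** The analysis set is described as patients with relevant data. A patient with two of three pain scores has relevant data, yet this method removes that patient.
- **The set analysed can depend on the Shapiro-Wilk result.** If normality is accepted and ANOVA is chosen, partial records go. If it is rejected and GEE is chosen, they stay. A test on the shape of the scores should not decide which patients count.
- **Patients with full records may differ from the rest.** If missing a reading is related to pain, and pain differs between arms, the comparison of complete cases can be biased.

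At stake are the acute pain and sleep comparisons. These are secondary outcomes.

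**Working it through.** The plan gives no figure on this point: no missing rate, no SD for acute pain or sleep, and no target effect for them. There is therefore nothing of the plan's own to reproduce. The sizes below rest on stated assumptions.

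**1. How many patients are lost.** If a share m of readings is missing at each visit, independently, the share with all three is (1 − m)³. With 64 per arm (section 2.11):

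| m per visit | complete share | complete patients of 64 |
|---|---|---|
| 2% | 0.98³ = 94% | 60 |
| 5% | 0.95³ = 86% | 55 |
| 10% | 0.90³ = 73% | 47 |

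**2. Power when 72 h scores are missing at random.** Assumed: 62 per arm, SD 1.8, within-patient correlation 0.6, true difference 0.8 at each time, and 10% of 72 h scores missing.

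- Variance of a patient's three-visit mean: 1.8² × (1 + 2 × 0.6)/3 = 3.24 × 0.7333 = 2.376.
- Complete cases: 62 × 0.9 = 55.8 per arm. SE = √(2 × 2.376/55.8) = 0.292, and 0.8/0.292 = 2.74. Power is about 78%.
- All readings, by likelihood: the variance of a 72 h score given the first two is 3.24 × (1 − 2 × 0.6²/1.6) = 3.24 × 0.55 = 1.782. The missing scores add (0.1/0.9) × 1.782/9 = 0.022. SE = √(2 × (2.376 + 0.022)/62) = 0.278, and 0.8/0.278 = 2.88. Power is about 81%.

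By noncentral t the unrounded values are 77.6% and 81.4%, a gap of about 4 points. Two simulations of this setting, 3,000 trials per scenario, gave 76% against 81% and 78% against about 80%, so 2 to 5 points is a fair range. With only 2% missing, the same formulas give 81.0% against 81.7%, a gap of less than 1 point.

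**3. Bias of the complete-case estimate.** Simulated with 64 per arm, correlation 0.6, a true difference of 0.50 SD at each visit, and 2,000 trials per setting. Full data give about 0.50 SD with power about 0.90. In the pain-related rows, missingness depends on the 48 h score, and the rate is nominal.

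| Assumed reason for missing | nominal rate | estimate (SD) | power |
|---|---|---|---|
| Unrelated to pain | 10% | 0.505 | 0.89 |
| Unrelated to pain | 20% | 0.50 | 0.83 |
| Unrelated to pain, more often in the active arm | 20% | 0.50 | 0.83 |
| Low pain, same rule in both arms | 10% | 0.44 | 0.83 |
| Low pain, same rule in both arms | 20% | 0.41 | 0.75 |
| High pain, same rule in both arms | 20% | 0.41 | 0.75 |
| Low pain, active arm only | 20% | 0.26 | 0.38 |
| High pain, active arm only | 20% | 0.65 | 0.99 |

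The estimate is unbiased when missingness has nothing to do with pain. It moves towards zero under either rule common to both arms, and away from zero when high-pain patients are missing from the active arm only.

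**4. What the mixed model does in the same situation.** In the setting of step 2, 72 h scores were made more likely to be missing after low 48 h pain (13%, 21% and 31% missing). The complete-case estimates were −0.747, −0.723 and −0.725 against a truth of −0.80. The mixed model gave −0.796, −0.793 and −0.808. Type I error was 4.2% to 5.5% for both methods.

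**The case against.** The strongest case on the other side has four parts.

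**The ANOVA branch is only an option, and pain scores may never reach it.** The same sentence allows t-tests, which use whatever is recorded at each time, and non-normal variables go to Mann-Whitney or GEE. Section 2.9 uses a numeric rating scale for in-hospital pain. If the outcome is an integer 0–10 score (an assumption; SD 1.8, control means of 3, 4 or 5, 64 per arm, 1,500 trials each), Shapiro-Wilk rejects normality in about 100% of simulated trials. This stands, and it is why the point is conditional. It does not clear the plan: sleep scores on a finer VAS could still pass. Nor is GEE a full answer, because unweighted GEE is in general not valid when missingness depends on earlier scores.

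**Readings may be nearly complete.** A reader might infer that patients who recover quickly go home before 72 h and lose all their scores. The documents do not support that. The Discussion hopes that "LP5 may facilitate faster postoperative recovery, improving overall patient rehabilitation and quality of life", and length of stay is an outcome, but nothing says anyone leaves before 72 h. Staff apply the patches through the third postoperative day, and Table 1 puts discharge after the 72 h column. This part stands in full.

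**The direction of bias is not fixed.** A reader might also infer that the acute effect must shrink. It does so only under some assumed mechanisms, and under another it grows. This also stands.

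**Models for each secondary outcome usually belong in the analysis plan.** Section 2.10 mentions a predefined statistical plan, which is not at hand. The article does, however, state both the method and the missing-data rule. The point concerns that stated combination, not an omission.

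**Conclusion.** The point holds in conditional form. If repeated-measures ANOVA is used for the 24/48/72 h pain or sleep scores, the ban on imputation removes every patient with a missing reading. This conflicts with the stated analysis set and makes the set depend on a normality test.

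The loss is about 2 to 5 points of power at an assumed 10% of 72 h scores missing at random, and under 1 point at 2%. Bias ranges from none to substantial, in either direction, according to a mechanism on which the documents are silent. The SD, correlation, effect and missing rates are all assumptions.

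Only secondary outcomes are touched; the primary regression is not. This is a cheap improvement, not a threat to the trial's main conclusion.

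**What to change.** In section 2.12, replace the choice between repeated-measures ANOVA and GEE for the 24/48/72 h pain and VAS sleep scores with one linear mixed model: arm, time and arm-by-time as fixed effects, unstructured covariance over the three times, and all available readings. State that it is used whatever the Shapiro-Wilk test shows, and that a patient with at least one reading is included. No imputation is needed, so the existing rule can stay. The model is valid when missingness depends on recorded scores, but not when it depends on the unrecorded score itself.

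The cost is one sentence and slightly more analysis work. No new data are needed, and the mixed procedure is available in the named SPSS version. If the data turn out complete, nothing is lost. Which contrast from the model enters the false-discovery-rate list is a separate choice and not part of this change.

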**Methods:**

This is a dual-center, randomized, double-blind, placebo-controlled trial involving 128 adult patients scheduled for knee arthroplasty. Participants will be randomly assigned, stratified by center, to either the LP5 group or the placebo group (n = 64 per group). The LP5 or placebo group will apply the patch 1 day before surgery and on postoperative days 1–3, with multimodal analgesia administered postoperatively. Multimodal analgesia will include intraoperative flurbiprofen axetil and postoperative patient-controlled sufentanil. The primary outcome is the pain subscale of the Western Ontario and McMaster Universities Osteoarthritis Index (WOMAC) at 3 months postoperatively. Secondary outcomes will include WOMAC stiffness, function, and total scales; Leeds Assessment of Neuropathic Symptoms and Signs (LANSS) Pain Scale; 36-Item Short Form Health Survey (SF-36); postoperative pain scores; Visual Analog Scale (VAS) sleep scores; postoperative sufentanil consumption; need for rescue analgesia; length of Post-Anesthesia Care Unit (PACU) stay; length of hospital stay; and 90-day mortality. Safety outcomes will include assessments of hypotension, hypertension, bradycardia, tachycardia, arrhythmia, interventions for haemodynamic events, headache, dizziness, nausea, vomiting, local skin allergy, wound infection, and toxic reaction. Data will be analyzed following a modified intention-to-treat approach.

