### 2.1 Study design and patients

This study is a dual-center, prospective, randomized, double-blind, placebo-controlled, parallel-group clinical trial. The trial will be conducted at the First Affiliated Hospital of Soochow University and Suzhou Xiangcheng People’s Hospital, enrolling a total of 128 patients. Recruitment is scheduled to take place from 16 July 2024 to 16 January 2025. The study flow diagram is shown in Figure 1.

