### 2.7 Randomization and blinding

An independent researcher will generate random numbers using an online tool (https://www.sealedenvelope.com/simple-randomiser/v1/lists) with a 1:1 allocation ratio, stratified by center. Randomization results will be stored in sealed opaque envelopes. Patients will be assigned to either the LP5 group or the placebo group. Postoperative care providers will prepare 5% lidocaine and placebo patches with patient numbers marked on the outer packaging. Patients, surgeons, anesthesia providers, outcome assessors, and statisticians will be blinded to group allocation.

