### 2.11 Sample size calculation

Based on previous studies, the standard deviation (SD) of the WOMAC Pain Scale prior to surgery is approximately 17, which corresponds to an 8–9 unit difference on the scale, representing the minimum clinically perceptible improvement (Wylde et al., 2015). To detect a 0.5 SD difference in WOMAC Pain Scale scores at 3 months postoperatively, with a two-sided α = 0.05 and 80% power, a sample size of 57 patients per group is necessary. Considering a potential dropout rate of 10%, we plan to enroll a total of 128 patients, with 64 patients in each group.

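### Randomisation is stratified by centre but centre is not in the primary regression; if centre predicts outcome, the standard error is slightly too wide and a little power is lost

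*Protocol article*

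**What the plan says.** Section 2.7 of the protocol article describes a randomisation list "with a 1:1 allocation ratio, stratified by center", and the Abstract repeats the stratification. No other stratification factor is named. Section 2.1 gives the sites: "The trial will be conducted at the First Affiliated Hospital of Soochow University and Suzhou Xiangcheng People’s Hospital, enrolling a total of 128 patients".

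For the analysis, section 2.12 states that the 3-month WOMAC pain score "will be analyzed via a linear regression model, adjusting for baseline variables including HADS scores, PCS scores, baseline WOMAC-pain scores, sex, age, and BMI". Centre is not in the list and is not mentioned anywhere else in that section. The same section adds a selection step: covariates with a p-value below 0.10 "will be retained in the final model". The bootstrap sensitivity analysis concerns the same regression and does not bring centre in. Section 2.10 refers to a predefined statistical plan, which is not available here.

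**The concern.** A factor used to stratify randomisation normally belongs in the analysis model. Stratification tends to balance the arms within each centre, so differences between centres add little or nothing to the true sampling error of the treatment contrast. A regression without centre leaves those differences in the residual and counts them as noise. The reported standard error is then larger than the true one, the confidence interval is wider than it need be, and the test rejects too rarely.

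The selection rule adds a second problem. Even if the open wording of the covariate list were taken to admit centre, its place would depend on an observed p-value. A design factor should be in the model because of the design.

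Power is at stake, and section 2.11 leaves none to spare, as shown below.

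**Working it through.** **Inputs from the protocol article.** Two centres, 1:1 allocation, stratified by centre (sections 2.1 and 2.7). Target: "To detect a 0.5 SD difference in WOMAC Pain Scale scores at 3 months postoperatively", "with a two-sided α = 0.05 and 80% power", with 57 evaluable and 64 enrolled per group (section 2.11).

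**Input not in the documents.** r, the share of residual variance in 3-month WOMAC pain that centre explains after the six listed covariates. Range assumed: 0 to 10%. The SD is taken as the residual SD before centre enters, so no gain from the six covariates is credited.

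**The plan's own figure.**
- n per group = 2 × (1.96 + 0.8416)² / 0.5² = 2 × 7.849 / 0.25 = 62.8, so 63 (64 with the t distribution), not 57.
- 57 follows only from 9/17 = 0.53 SD, the top of the stated 8–9 unit range: 2 × 7.849 / 0.529² = 56.01, rounded up to 57.
- The dropout step agrees: 57 / 0.9 = 63.3, so 64.
- Power at 57 per arm and 0.5 SD: 0.5 / √(2/57) = 2.669; Φ(2.669 − 1.96) = 76.1% (75.4% with the t distribution).

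The mismatch in 57 is a separate matter. It is used here only to set the baseline power.

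**Effect of leaving centre out, arms balanced within centre.**
- Reported SE / true SE = 1 / √(1 − r)
- Actual two-sided type I error = 2 × [1 − Φ(1.96 / √(1 − r))]
- Power without centre = Φ[(2.669 − 1.96) / √(1 − r)]
- Power with centre = Φ[2.669 / √(1 − r) − 1.96]
- Gap between centre means, equal-sized centres = √(r / 0.25) SD

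| r | Gap (SD) | SE too large by | Type I error without centre | Power without | Power with |
|---|---|---|---|---|---|
| 0 | 0 | 0% | 5.0% | 76.1% | 76.1% |
| 2% | 0.28 | 1.0% | 4.8% | 76.3% | 76.9% |
| 5% | 0.45 | 2.6% | 4.4% | 76.7% | 78.2% |
| 10% | 0.63 | 5.4% | 3.9% | 77.3% | 80.3% |

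**Simulation check.** Least squares with and without centre, 57 per arm, arms balanced within two near-equal centres, 40,000 simulated trials per setting:
- r = 5%: type I error 4.3% without centre and 4.8% with it; power 76.1% and 77.6%.
- r = 10%: type I error 3.8% and 5.0%; power 76.3% and 79.6%.

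The simulation uses t tests, so its power sits slightly below the normal approximation. Splitting the centres 43 to 14 per arm gave nearly the same results.

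**The case against.** **The loss is conditional and may be nil.** The documents give no centre effect. The six covariates may already absorb differences in case mix between the hospitals. A reader might infer from the design alone that the standard error is too wide and power is lost. The documents do not support that: at r = 0 nothing changes. This objection stands, and the point is worded accordingly.

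**The upper end of the range is demanding.** With equal-sized centres, r = 10% puts the centre means 0.63 SD apart, more than the 0.5 SD treatment effect the trial is built to detect. At 2% the gain is about half a power point. This stands too.

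**A centre effect should not be presumed from separate teams.** A reader might suppose that each hospital has its own surgeons and care teams. The article does not say so. Sections 2.8 and 2.9 set one surgeon-experience threshold and common patch and anaesthetic procedures, which would tend to reduce centre differences.

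**Balance within centre is not guaranteed.** Section 2.7 names stratification but no blocking. Without blocking, the balance and the conservatism are weaker. Adjusting for centre would still recover power.

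**The covariate list is open and a fuller plan may exist.** The word introducing the list leaves room for other covariates, and section 2.10 points to a statistical plan. But section 2.12 does fix six named covariates and a retention rule, and nothing in the article puts centre in the model or protects it from that rule.

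**A dropped centre term would usually cost little.** This is fair. With 114 evaluable patients and about 105 residual degrees of freedom, the expected t for centre is roughly √(105 × r / (1 − r)): 1.5 at r = 2% and 2.4 at r = 5%, against a 10% critical value of 1.66. The rule would therefore tend to remove centre only where it explains little. The case for exempting centre is mainly one of matching the analysis to the design and avoiding a data-driven choice.

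**Conclusion.** The point holds as a modest matter of efficiency and consistency with the design. The trial randomises by centre and specifies a primary regression that omits it. If centre predicts 3-month WOMAC pain after the listed covariates, and the arms are balanced within centre, the test is mildly conservative. The gain from adding centre is about 0.6, 1.5 or 3.0 power points for r of 2%, 5% or 10% (76.9 − 76.3, 78.2 − 76.7, 80.3 − 77.3), and zero if centre is not prognostic.

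A reader might go further and conclude that the primary analysis is biased or its type I error inflated. Neither follows: omitting a factor balanced by design leaves the estimate unbiased and moves the error rate below 5%, not above it.

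The figures rest on the assumed r, on within-centre balance, and on 57 evaluable patients per arm. The change is worth making because it is nearly free and the planned power at 0.5 SD is already about 76%, but the trial's validity does not depend on it.

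**What to change.** In section 2.12, add centre as a fixed term in the primary linear regression and state that it stays in the model whatever its p-value, so that the p<0.10 rule does not apply to it. Carry the same model into the bootstrap sensitivity analysis.

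For secondary outcomes, include centre where the planned analysis is a regression-type model, such as repeated measures ANOVA or GEE. The t, Mann-Whitney, chi-square and Fisher tests in that section take no centre term, and this point does not require replacing them.

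The cost in the primary regression is one degree of freedom. No new data are needed, because each patient's centre is known from the stratified randomisation. The change should be fixed before unblinding so that adjustment for centre does not become a post hoc choice.
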